### Data management

A codebook for all study variables is created. A trained research assistant enters data into SPSS, verified weekly. Data cleaning uses frequency counts for all variables at each data collection point to check for outliers. All possible strategies are employed to prevent missing data, including in-person data collection by trained research assistants. Missing data is considered analytically through full information maximum likelihood (FIML) procedures available in standard software for generalized mixed to reduce potential bias and loss of power that would otherwise occur when using traditional listwise deletion for missing data [42]. The codebook does not include paper case report forms (CRFs). Instead, we use the HIPPA-Compliant REDCap database as the electronic data capture for the study. We export the REDCap data or CSV files to be analyzed using SPSS and R for data analysis.

### Confidentiality

Participants’ data is stored using a participant identification number at the screening time. According to research guidelines, the key to the identification code list is only available to the research team during the study and documented and safeguarded by the principal investigator. Only personnel directly related to the project or the University human subject oversight office has access to the data. All data will be reported as group data.

### Data analysis

Univariate descriptive statistics will be used to describe the characteristics of the sample, gait, balance, and lower extremity muscle strength. Values for the exercise will be divided into quartiles to determine the uppermost and lowest values to compare with published literature [43]. Analysis of univariate statistics allows us to assess the normality of distributions for our continuously distributed variables, patterns of missing values, and whether univariate outliers may be present that could distort subsequent bivariate and multivariate analyses. By implementing appropriate link functions in the generalized linear model framework, distributional assumptions, such as normality and potential non-linearity, will be addressed. Potential non-normality may also be addressed by implementing robust estimation through Huber-White standard errors (i.e., “sandwich” estimators), also implementable in the generalized mixed model framework. We do not aggregate outcomes. Instead, we are looking at a specific change of each metric between baseline and 16 weeks and comparing study groups. In addition, we will perform baseline comparisons between groups. Any unbalance covariate(s) will be adjusted in multivariate analyses. We do not plan any subgroup analyses.

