## Methods/design

### Study design

A two-group, 16-week randomized clinical trial is designed to address persistent taxane-induced peripheral neuropathy in women treated for invasive breast cancer. The study design is a parallel, two-arm, randomized controlled trial with a 1:1 ratio between groups.

A sample of 312 women who completed taxane-based chemotherapy for breast cancer and have symptomatic neuropathy (≥ 3 on a neuropathy visual analog scale VAS) ≥ 6 months following completion of taxane-based chemotherapy will be recruited. Participants are randomized to either a Home-Based Physical Activity Intervention (B-HAPI) for persistent taxane-induced neuropathy or an educational attention control group. Assessment of gait, balance, strength of lower extremity muscles, neuropathy symptoms, and nerve conduction velocity will be collected at baseline (prior to randomization) and 16 weeks. The participant flow diagram is shown in Fig. 1. The protocol follows the Standard Protocol Items: Recommendations for Interventional Trials (SPIRIT) Figure (Fig. 2) and Checklist (Additional File 1) [16].

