#### SEM approach

The variance population parameters recommended by Muthén and Muthén were used (intercept variance = 0.50, slope variances (intervention = 0.10, intercept and slope covariances = 0.00), and residual variance at all waves = 0.50). Homogeneity of variances was assumed between the treatment and control groups. To reflect effective randomization of participants to conditions, we modeled no mean difference between treatment and control conditions at baseline. The differences in slopes between the treatment and control conditions during the intervention period are the focal parameter to be adequately powered. Given alpha = .05, a two-tailed hypothesis test, and the view that a power value of .80 will be adequate to detect a treatment effect, a minimum sample of *N* = 312 participants (based on recruitment of 2 or more participants per week for 3 years) with 20% attrition and 10% periodic non-response, is needed.

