#### Intention to treat (ITT) approach

A full-information maximum likelihood approach for an intent-to-treat analysis is used, and a Monte Carlo simulation with 10,000 replications suggests we will be able to detect a minimum standardized effect of 0.30 with a probability of correctly rejecting a false null (power) of .81. If the recruitment rate is closer to 3 per week resulting in a sample of *N* = 468, the minimum detectable standardized effect is 0.25. By including additional control variables (all ES’s = .10), the minimum detectable effect sizes decrease to 0.27 and 0.22, respectively. A recent and relevant meta-analysis reported effect sizes for exercise intervention effects on similar outcomes ranging from ES = 0.30 to ES = 0.84 [30]. We will compare the mean differences between groups and the rates of change (slopes) between the groups.

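### The arms are to be compared on change from baseline (or the equivalent two-point slope); a pre-specified week-16 comparison adjusted for the outcome's own baseline estimates the same effect at least as precisely

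*Protocol article*

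**What the plan says.** The Data analysis section of the protocol article describes the comparison of arms in these terms: "we are looking at a specific change of each metric between baseline and 16 weeks and comparing study groups". It also plans baseline comparisons between groups, with adjustment for any covariate found unbalanced.

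The sample-size text works with slopes. Under SEM approach: "The differences in slopes between the treatment and control conditions during the intervention period are the focal parameter to be adequately powered". Under Intention to treat (ITT) approach: "We will compare the mean differences between groups and the rates of change (slopes) between the groups". That subsection also mentions additional control variables but does not name them.

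Study design, Sample size, and Assessment and collection of outcomes all give two assessments only, at baseline and 16 weeks. The power model assumes no difference between arms at baseline. Full-information maximum likelihood (FIML) is invoked for the intent-to-treat analysis and for missing data. The article does not say that the analysis model holds the baseline means equal across arms, or that the outcome's baseline value enters as a covariate.

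**The concern.** With two time points, a linear slope is (week 16 minus baseline)/16. Comparing slopes is therefore comparing changes on another scale, and listing both adds nothing.

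A change score also gives the baseline value a coefficient of exactly one. If the true regression of the week-16 value on baseline has a coefficient below one, subtracting the whole baseline adds noise. Randomization makes the expected baseline means equal, so the baseline can be used as a covariate without altering the effect being estimated. Adjusting only for variables that look unbalanced does not replace this, because the benefit comes from how well baseline predicts the outcome, not from chance imbalance.

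At stake is precision on the gait, balance and strength outcomes, obtainable from measurements already being taken. Trial status reports 33 participants recruited against a target of 312, so precision that needs no extra participants is worth having.

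**Working it through.** **Inputs** (protocol article, Sample size and its subsections, unless noted):
- intercept variance 0.50, slope variance 0.10, intercept-slope covariance 0, residual variance 0.50 at each wave;
- two-sided alpha .05, target power .80;
- N = 312 (Study design), allocated 1:1, so 156 per arm;
- standardized effect 0.30 with stated power .81;
- 20% attrition and 10% periodic non-response;
- test-retest r from 0.70 to 0.97 (Table 4). Using these as a guide to the 16-week correlation is my assumption. They are an upper guide, since short-term reliability usually exceeds a 16-week correlation.

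**General result.** Let v0 and v1 be the variances at weeks 0 and 16, and c their covariance.
- Change score: Var = v0 + v1 − 2c.
- Week 16 adjusted for baseline: Var = v1 − c²/v0.
- Difference: (v0 − c)²/v0, which is never negative. It is zero only if c = v0, that is, if the regression of week 16 on baseline has slope 1.

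**Planning components, 0 to 16 weeks coded as one unit.**
- v0 = 0.50 + 0.50 = 1.00; v1 = 0.50 + 0.10 + 0.50 = 1.10; c = 0.50.
- Change: 1.00 + 1.10 − 1.00 = 1.10.
- Adjusted: 1.10 − 0.25/1.00 = 0.85.
- Ratio 0.85/1.10 = 0.773, or 23% less variance. Since 1.10/0.85 = 1.29, this is worth about 29% more participants.

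**Same components, slope variance taken per week.** The Sample size text gives weeks since baseline as the time metric.
- v1 = 0.50 + 256 × 0.10 + 0.50 = 26.6; c = 0.50.
- Change: 1.00 + 26.6 − 1.00 = 26.6.
- Adjusted: 26.6 − 0.25 = 26.35.
- Ratio 0.99, or about 1% less.

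**Equal variances, correlation r.** The ratio is (1 − r²)/[2(1 − r)] = (1 + r)/2.

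| r | ratio | variance saved |
|---|---|---|
| 0.50 | 0.75 | 25% |
| 0.70 | 0.85 | 15% |
| 0.87 (balance composite) | 0.935 | 6.5% |
| 0.97 | 0.985 | 1.5% |

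**The plan's power figure.** This uses one-unit coding, an effect of 0.30 baseline standard deviations and complete-case formulas. Power = Φ(0.30/√(2·Var/n) − 1.96), with n per arm.

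| Loss | n per arm | Change | Adjusted |
|---|---|---|---|
| none | 156 | .714 | .820 |
| 20% | 124.8 | .618 | .729 |
| 28% = 1 − 0.80 × 0.90 | 112.3 | .573 | .684 |

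The stated .81 is not reproduced at the stated attrition. The highest two-sided value found with 20% loss was .769, for the adjusted analysis with the effect scaled to the week-16 standard deviation.

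**Simulation.** With 10,000 replicates, one-unit coding and 20% loss, power was .610 for change and .719 for adjusted. Both estimators averaged about 0.30, so they estimate the same effect. The empirical variance ratio was 0.77 to 0.78 across the loss rates tried. At 28% loss, a separate run that kept the baseline values of participants missing at week 16, with baseline means left free, gave .600 for the slope comparison. It gave .575 for complete-case change and .678 for the adjusted analysis.

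**The case against.** The strongest reply is that the sentence in Data analysis mainly says that metrics are analysed singly and not aggregated, so it need not fix an unadjusted change-score estimator. A FIML model with equal baseline means would already have essentially the recommended precision, and model detail may sit in an analysis plan not shown. Part of this stands: the article does not exclude such a model. But both that sentence and the powered parameter describe a change contrast. The equal-baseline assumption appears only in the power model, and the only covariate rule stated depends on observed imbalance.

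Four stronger readings are tempting, and the document does not support them.
- *That .81 is reached only with baseline adjustment, or is wrong.* With the stated attrition, adjustment does not reach .81 either in the variants tried. The effect's standardizer, the time scaling and the missing-data pattern are not given, so the figure can be neither confirmed nor refuted.
- *That a quarter of the information is being given away.* The 23% depends on one-unit time coding and on generic recommended variances, not estimates for these outcomes. The complete-case .573 (.575 simulated) also understates a FIML analysis; .600 is the fairer comparator at 28% loss.
- *That the growth model cannot be identified from two waves.* SEM approach sets the intercept-slope covariance to zero and gives one residual variance for all waves. That leaves three variance parameters for three observed moments. The slope difference itself is estimable in any case.
- *That two results per outcome compete with no deciding rule.* The slope difference is named as the powered quantity. If mean differences refers to differences in mean change, there is only one result. The wording is redundant rather than contradictory.

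**Conclusion.** The point holds as a matter of efficiency. The article describes a change contrast, restates it as slopes on two time points, and does not pre-specify adjustment for the outcome's own baseline value. The adjusted week-16 difference estimates the same effect and in large samples cannot be less precise.

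The gain may be anything from about 1% to about 23% on the planning components, depending on the time unit. If pre-post correlations approach the test-retest values, it would be 1.5% to 15%; lower correlations would give more. This rests on randomization, on correlations not yet known for this population, and on large-sample variances. No bias is shown, and the change analysis remains valid. This is a free improvement, not the correction of an error.

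**What to change.** For each outcome, pre-specify one contrast: the week-16 difference between arms from a linear model with arm and the baseline value of that outcome. Equivalently, use a two-wave FIML model with a common baseline mean and an unstructured covariance, which keeps participants who have only one measurement. Make the adjustment unconditional, not dependent on the baseline comparison. Drop the separate slope comparison and show mean change by arm descriptively only. If power is restated, base it on this model and give the time unit, the standardizer and the assumed loss.

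The cost is analysis wording. No new data, visits or participants are needed, and the change should be made before outcomes are compared by arm.

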### Assignment of interventions: allocation and blinding

Randomization to study groups is achieved using a computer-generated random numbers list (REDCap software, Nashville, TN) by the study statistician. A sealed, consecutively numbered, opaque envelope containing the subject’s group assignment (Exercise Intervention or Educational Attention Control) is opened to reveal the participant’s study group assignment. The study statistician generates the allocation sequence. The project manager enrolls participants, and the research assistant assigns participants to intervention groups. It is not an open-label study. The PI, data collectors, and the principal statistician are blinded. The data collector is blinded to the study group assignment. There is no unblinding procedure. No blocking or stratification is used.

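### Adjustment covariates are to be picked by observed baseline imbalance, which under simple randomization selects on chance, leaves the adjusted models open and forgoes precision

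*Protocol article*

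**What the plan says.** Protocol article, Data analysis: the arms are to be compared at baseline ("In addition, we will perform baseline comparisons between groups"), and the next sentence turns the result into a modelling rule: "Any unbalance covariate(s) will be adjusted in multivariate analyses". The same section analyses each metric's change from baseline to 16 weeks separately.

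Two other places bear on this:

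- **Allocation.** The Study design section describes a "parallel, two-arm, randomized controlled trial with a 1:1 ratio between groups". The allocation section adds: "No blocking or stratification is used". There are therefore no design factors that would fix a minimum adjustment set.
- **Power.** The Intention to treat (ITT) approach section says that including further control variables lowers the detectable standardized effect from 0.30 to 0.27 at N = 312, and from 0.25 to 0.22 at N = 468.

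Nothing else in the article limits or overrides the imbalance rule.

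**The concern.** With simple randomization properly carried out, the arms differ at baseline only by chance. A baseline comparison therefore identifies covariates that happened to fall unevenly, not covariates that predict gait, balance or strength. Adjustment helps when a covariate is prognostic, and that is true whether or not it looks balanced.

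Three things follow from selecting on imbalance:

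- The adjusted model for each metric is settled only once the baseline data are seen by arm, and the analyst must judge what counts as unbalanced. The Bonferroni-Holm correction planned in the Outcomes section works across outcomes. It does not cover alternative models for one outcome.
- Prognostic covariates that look balanced are left out, and their precision is lost.
- The power section's gain from control variables requires prognostic covariates to be in the model every time. This rule does not ensure that.

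**Working it through.** **1. The plan's own figure, for context.** At N = 312 the plan expects to "detect a minimum standardized effect of 0.30 with a probability of correctly rejecting a false null (power) of .81". Inputs from the SEM approach section: intercept variance 0.50, slope variance 0.10, then "intercept and slope covariances = 0.00), and residual variance at all waves = 0.50". Assume time is coded 0 and 1.

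- Baseline variance: 0.50 + 0.50 = 1.00.
- Follow-up variance: 0.50 + 0.10 + 0.50 = 1.10.
- Covariance: 0.50.
- Variance of follow-up given baseline: 1.10 − 0.50²/1.00 = 0.85.
- Variance of change: 0.10 + 2 × 0.50 = 1.10.

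For an effect of 0.30 with 156 per arm and no attrition, power is 0.82 with baseline as a covariate and 0.71 with a plain change score. With 20% attrition the baseline-adjusted figure is 0.73 to 0.77, depending on how the effect is scaled. The standardization behind .81 is not given, so these figures do not test it. They do show that, on the plan's own variances, how the baseline value enters the model matters.

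**2. What the claimed covariate gain requires.** At fixed N, alpha and power, the detectable effect is proportional to the residual SD.

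- N = 312: 0.27/0.30 = 0.90. The residual variance falls to 0.90² = 0.81 of its value, so the covariates must explain about 19% of it.
- N = 468: 0.22/0.25 = 0.88, and 0.88² = 0.77, so about 23%.

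**3. How often chance alone would flag something.** The article gives neither a threshold nor a candidate list. Take p < 0.05 and k independent covariates as an illustration: P(at least one flag) = 1 − 0.95^k.

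| k | P(at least one) |
|---|---|
| 5 | 23% |
| 10 | 40% |
| 20 | 64% |

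These are probabilities that the model changes. They are not a bias or an error rate.

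**4. What the rule does to the estimate.** This is a simulation with 6,000 replicates per scenario. It uses 250 completers (312 × 0.80 ≈ 250). The other inputs are assumptions outside the document: 10 independent baseline covariates, of which two predict the outcome (r = 0.5 and 0.4), and imbalance defined as p < 0.05.

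| | No adjustment | Imbalance rule | Two prognostic covariates pre-specified |
|---|---|---|---|
| Type I error | 0.051 | 0.039 | 0.046 |
| Power, true effect 0.30 SD | 0.67 | 0.67 | 0.87 |
| Mean standard error (effect 0.30) | 0.1263 | 0.1259 | 0.0975 |
| Actual SD of the estimate (effect 0.30) | 0.1264 | 0.1203 | 0.0977 |

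Some covariate was selected in 40% of trials, but one of the two prognostic ones in only about 9%. The rule's mean standard error was 0.1259/0.1263 = 0.997 of the unadjusted one. The actual spread fell somewhat more (0.1203/0.1264 = 0.95), and because the reported standard error does not reflect this, the test is slightly conservative. Pre-specification reduced the standard error to 0.0975/0.1263 = 0.77.

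**5. Allowing for a baseline value already in the model.** Step 1 implies a baseline to follow-up correlation of 0.50/√(1.00 × 1.10) = 0.48, close to the r = 0.5 covariate in step 4. If that one is already used, residual variance is 1 − 0.25 = 0.75 without the second covariate and 1 − 0.25 − 0.16 = 0.59 with it. At 125 per arm, power = Φ(0.30/(√variance × √(2/125)) − 1.96):

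- 0.75: Φ(2.74 − 1.96) = 0.78.
- 0.59: Φ(3.09 − 1.96) = 0.87.

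The precision forgone then shrinks to 0.78 against 0.87, again on an assumed correlation for the second covariate.

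**The case against.** The strongest reply is that little demonstrable harm follows. Four parts of it stand.

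- **No inflation of false positives.** A reader might infer that a data-driven covariate rule raises the type I error. Applied mechanically in the simulation, it gave 0.039, and power was no lower than with no adjustment.
- **The baseline outcome is partly used already.** The plan analyses change, powers a two-wave slope difference and uses full-information maximum likelihood. That is not identical to baseline adjustment, but it recovers part of the precision, and the 0.67 against 0.87 contrast gives no credit for it.
- **The primary estimate.** A reader might infer that it is left unfixed. The article does not say whether the covariate-adjusted analyses are primary or supportive, so that goes further than the text.
- **The flag probabilities.** A reader might take 64% as the size of the problem. The threshold and the number of variables are not in the article, nothing says that the outcome metrics are the candidate covariates, and several gait metrics are clearly correlated.

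It is also fair that a covariate list and a definition of imbalance may sit in an analysis plan that is not shown, so their absence is no fault here. What the reply does not reach is the stated rule. A comparison without significance tests, or with another threshold, would still select on chance.

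**Conclusion.** The point holds as a moderate one. The article states a rule that selects covariates by chance imbalance. The adjusted model for each metric therefore depends on the realised data, and the rule cannot deliver the reduction from 0.30 to 0.27 that the power section attributes to control variables. That reduction needs about 19% of residual variance explained, in every trial.

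The harm is discretion and forgone precision. Its size cannot be fixed from the document. In the illustrations power is 0.67 under the rule against 0.87, or 0.78 against 0.87 once a baseline value is credited, and both contrasts rest on assumed prognostic correlations. The conclusion that imbalance is chance assumes that randomization was properly implemented. A reader might also infer from the context figures that the stated power of .81 is wrong. The effect's standardization is not given, so the document does not support that.

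**What to change.** Replace the imbalance sentence with a fixed rule:

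- Whatever the observed balance, each outcome model adjusts for the baseline value of that outcome, either as a covariate or through a longitudinal model that constrains the baseline means to be equal.
- It also adjusts for a short list of covariates chosen on prognostic grounds and fixed before unblinding. Age, time since taxane completion and the neuropathy VAS are possible candidates, because eligibility screening must ascertain them. They are only examples: the article does not show that any of them predicts gait, balance or strength.
- Baseline characteristics are presented by arm descriptively and are not used to select covariates.
- The power section's control variables should be this same list.

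The cost is wording and a few degrees of freedom per model. No new visit or assessment is needed, and the Trial status section reports only 33 of the planned 312 participants recruited at that version.
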